## Abstract

Background

Acute respiratory distress syndrome (ARDS) affects a significant proportion of ICU patients and has a high mortality rate. The inflammation of the alveolar-capillary membrane is pathognomonic and characterized by increased capillary permeability and pulmonary edema. A safe, readily available anti-inflammatory agent delivered directly to the lungs could be a promising therapeutic approach. All these properties apply to nebulized furosemide.

Objectives

The primary objective of this study is to analyze 28-day all-cause ICU mortality while the secondary objectives include assessing hospital mortality, ICU and hospital length of stay (LOS), ventilator-free days at 28 days, successful extubation rate, and adverse events.

Methods

A double-blind, placebo-controlled, parallel-arm superiority RCT using an intention-to-treat (ITT) analysis to assess whether nebulized furosemide reduces mortality in adult mechanically ventilated ARDS patients will be employed.

Results

The results of descriptive and inferential analyses will be tabulated, and the significant results will be presented.

## Introduction

Acute respiratory distress syndrome (ARDS) is usually defined as rapidly evolving hypoxemia due to pulmonary edema originating from causes other than cardiogenic such as increased alveolar-capillary permeability [1,2]. The Berlin Definition, established in 2012 by an expert panel, provides an objective clinical framework for defining ARDS [1]. ARDS encompasses a wide spectrum of risk factors and/or causes that could be generally divided into direct and indirect causes [3], direct causes may include aspiration, pneumonia, lung contusion, inhalational injury, and near drowning [4], whereas examples of indirect causes include sepsis, transfusion, hemorrhagic shock [4], pancreatitis, burns, drugs, or toxins [5]. Some studies have also associated tobacco and alcohol use, hypoalbuminemia, air pollution, and recent chemotherapy with increased risk of ARDS [2,6,7].

ARDS accounts for 10% of ICU admissions and 25% of ventilated patients, affecting 3 million people annually worldwide [4,8]. The prevalence may rise with broader definitions that include high-flow nasal oxygen patients [9]. Reported mortality rates remain as high as 30%-40% or more [2,8]. This may be because of the myriad of causes and risk factors of ARDS [2], it could also be due to the difficulty in distinguishing ARDS from its risk factors as the cause of death [10], the challenging setting of ARDS management, which usually encompasses multiple organ failure, but possibly more important, due to the lack of definitive therapy, and the management being mainly supportive [11].

A recent multicenter phase II randomized controlled trial (RCT) explored the effect of nebulized furosemide in intubated COVID-19 patients [12]. The study did not reach its target sample size due to a lack of recruitment by early 2023; consequently, all of its objectives did not reach the level of statistical significance. However, there were obvious trends of the beneficial effects of nebulized furosemide. The intervention group had a higher change from day one to day six of partial pressure of oxygen in arterial blood (PaO2) to fraction of inspired oxygen (FiO2) ratio (P/F ratio), lower 60-day mortality, lower hospital length of stay (LOS), and longer ventilator-free days, with no reported adverse events.

We hypothesize that the use of nebulized furosemide in adult, mechanically ventilated patients with ARDS admitted to the ICU may decrease 28-day mortality.

Rationale of nebulized furosemide in ARDS

ARDS is characterized by an acute onset of inflammatory lung injury, with impaired gas exchange and non-compliant “stiff” lungs [13]. A histologic hallmark of ARDS is capillary endothelial injury and diffuse alveolar damage, manifesting typical inflammation, apoptosis, and necrosis of pulmonary epithelial and endothelial cells, leading to increased alveolar-capillary permeability, ultimately resulting in alveolar edema and proteinosis, and may also include alveolar hemorrhage, pulmonary capillary congestion, interstitial edema, and hyaline membrane formation [14].

An ideal therapeutic agent should possess broad anti-inflammatory activity. Several agents, such as corticosteroids and immunosuppressants, exhibit these properties. However, their systemic administration has drawbacks such as myopathy and decreased immunity, in addition to being expensive, difficult to produce, and a lack or shortage in some countries [12]. Hence, the ideal therapy would also have to be cost-effective, readily available, associated with low toxicity, and could be directly delivered to the lung tissue [12].

Furosemide (4-chloro-5-sulfamoyl-N-furfuryl-anthranilate) is a powerful loop diuretic that acts on the thick portion of the ascending limb of the loop of Henle by binding to the sodium-potassium cotransporter. It has a short half-life and low bioavailability, in addition to being inexpensive and readily available [12,15]. Nebulized furosemide has been used for a variety of lung conditions, such as dyspnea and bronchial asthma [16,17], owing to not only the presumed higher concentrations delivered to the pulmonary tissue via nebulization compared to systemic or oral routes but also due to its anti-inflammatory characteristics [12].

Furosemide is an analog of 3-hydroxyanthranilic acid (3HA) (a tryptophan metabolite). 3HA is diffusely found in the human body and can suppress T-cell responses [18], thus suppressing the production of several inflammatory cytokines [19]. In vitro, furosemide was reported to reduce the lipo-polysaccharide-induced release of inflammatory cytokines, such as interleukin-6 (IL- 6) and tumor necrotizing factor (TNF), in addition to inducing macrophage phenotypic changes from the pro-inflammatory M1 state to the anti-inflammatory M2 state and promoting the release of anti-inflammatory cytokines such as arginase [20]. The reduction of inflammatory cytokines was also reported by clinical animal studies [21]. Similarly, human clinical studies demonstrated the beneficial effect of nebulized furosemide in the treatment of pulmonary edema [15], its effectiveness in reducing pulmonary epithelial permeability in smokers, and even restoring it to normal in asthmatic patients [[22]. Hence the use of nebulized furosemide in the treatment of several lung conditions and symptoms such as bronchial asthma, dyspnea, breathlessness, and chronic obstructive pulmonary disease (COPD) in many studies, with promising results [23-26].

## Materials and methods

Study design

This is a single-center, double-blind, placebo-controlled, parallel arms, superiority randomized clinical trial. The maximum duration of the intervention will be 28 days while the duration of follow-up will be till hospital discharge. The study will be conducted in the ICU of the largest government hospital in the central region of Saudi Arabia. The ICU has 110 beds, fully equipped with invasive and non-invasive monitoring and ventilation capabilities. It is covered round the clock by intensivists, with a nurse-patient ratio of 1: 1.

Inclusion and Exclusion Criteria

Inclusion criteria: Adults (≥18 years), ICU admission, mechanical ventilation for <7 days, and ARDS diagnosed within 24 hours per the Berlin Definition [1], which includes: a) Chest x-ray showing bilateral opacities, not fully explained by effusions, lobar/lung collapse, or nodules; b) Respiratory failure not fully explained by cardiac failure or fluid overload, and exclusion of hydrostatic edema (by echocardiography); c) Oxygenation and ventilator settings matching one of the three categories of ARDS: Mild: 200 mmHg < PaO2/FIO2 ≤ 300 mmHg with positive end-expiratory pressure (PEEP) or continuous positive airway pressure (CPAP) ≥ 5 cm H2O. Moderate: 100 mm Hg < PaO2/FIO2 ≤ 200 mm Hg with PEEP ≥ 5 cm H2O. Severe: PaO2/FIO2 ≤ 100 mm Hg with PEEP ≥ 5 cm H2O.

Exclusion criteria: Pregnant or lactating ladies; Patients who are not expected to survive more than 48 hours, according to the treating team; Mechanical ventilation is expected to continue for less than 48 hours (due to rapid recovery) according to the treating team; Advanced directive of Do Not Resuscitate (DNR); Refusal to participate in the trial by the patient or official surrogate; Known allergy to furosemide; Previous enrollment in the trial (a patient can only be enrolled once).

Study objectives

The primary objective is 28-day mortality in the ICU, starting from the day of randomization. Secondary objectives include: All-cause hospital mortality, ICU and hospital length of stay (LOS), the difference in P/F ratio between day one and day seven (not to be calculated for patients who are censored before seven days), 28 days ventilator-free days (VFD) (defined as days without mechanical ventilation till day 28 starting from day of enrollment, as long as the patient is alive); patients still mechanically ventilated at day 28, or died by day 28, will be assigned zero VFD. If the artificial airway is shifted from endotracheal tube to tracheostomy, they will still be considered mechanically ventilated until they are liberated from mechanical ventilation and are spontaneously breathing. With respect to a successful extubation rate, defined as extubated and not requiring re-intubation for 72 hours, tracheostomy is not considered successful extubation. Examples of adverse events will be hypersensitivity reactions - of any magnitude, abnormal lab investigations, specifically electrolytes and renal function tests, and volume of urine output.

Enrollment, randomization, and allocation concealment

After obtaining the informed consent of a legal guardian, randomization will be obtained via a phone call providing a study code, without breaking the concealment of allocation. Randomization will be performed using variable block sizes (4, 6, or 8), stratified by ARDS severity (mild, moderate, severe).

Blinding

Furosemide and saline are identical in appearance, color, and solution characteristics. The investigational medication will be prepared by an independent pharmacist in identical vials, labeled only with study code and patient identifiers, and delivered to the clinical area. The flow of patients' enrollment is depicted in Figure 1.

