Assuming a mortality rate of 40% in the control group [2,8], and aiming to detect an effect size of 10% absolute reduction in mortality in the intervention group with a power of 80% and type I error rate of 5%, we estimated the sample size to be 712 patients (356 in each group), with 10% inflation to compensate for possible loss of follow-up (patients transferred to other healthcare facilities), we plan to recruit a total of 784 patients, allocated in a 1: 1 ratio as 392 patients in each group.

Statistical plan

Intention-to-treat (ITT)-based analysis: Data of the patients will be analyzed in the group to which they were randomized, regardless of the actual intervention they received. Continuous variables will be summarized as mean ± standard deviation (SD) or median and interquartile range (IQR) depending on the normality assumption, tested for by the Shapiro-Wilk normality test. Discrete variables will be summarized as frequency (count) and percentage. Time-to-event data will be 28-day mortality as the event and duration since randomization as the time variable, with right censoring.

For the primary outcome, comparison between both groups for 28-day mortality will take place by the chi-square test of association, for secondary outcomes, groups will be compared by the chi-square test of association or Fisher’s exact test, according to data count in each cell of the two by two contingency table, while continuous variables will be compared between groups by the student's t-test or the non-parametric Wilcoxon Rank-Sum test.

We will perform a survival analysis using the time-to-event data, in the form of a Kaplan-Meier Survival curve as compared by the log-rank test.

As a sensitivity test for the primary outcome, we will fit two regression models. First will be a multinomial logistic regression model, using backward elimination to retain only variables with p-value < 0.1 and the severity of ARDS as the multinomial levels in the model. A multivariable proportional hazard model (Cox regression) will be carried out in a similar way, utilizing days from randomization to event as the time variable. Additionally, we will present a per-protocol analysis of the primary outcome.

A priori subgroup analyses will examine the primary outcome with regard to sex, the median age of the cohort, ARDS severity, and adjunct and rescue therapies used (such as corticosteroids, prone positioning, and ECMO).

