## Results

All results of group comparisons will be presented with either mean or percent difference, along with the corresponding 95% confidence interval (CI). The main results will be presented within the text of the results section while all results will be presented in table formats; the first dummy table outlines the baseline characteristics of the enrolled patients and the second dummy table will include the outcomes (dummy Tables 1, 2).

**Table 1 TAB1:** Dummy table showing baseline characteristics SOFA = Sequential Organ Failure Assessment, CFS = Clinical Frailty Scale, BMI = Body Mass index, CKD = Chronic Kidney Disease, CLD = Chronic Liver Disease, CPD = Chronic Pulmonary Disease, CHD = Chronic Heart Disease, PaO2 = Arterial Partial Pressure of Oxygen, FiO2 = Fraction of Inspired Oxygen, P/F = PaO2 / FiO2, PEEP = Positive End-Expiratory Pressure, CPAP = Continuous Positive Airway Pressure, ARDS = Acute Respiratory Distress Syndrome

Variable (mean±SD) or (n,%)	Furosemide Group (n=………)	Control Group (n=………..)
Age (years)		
Sex (Females)		
SOFA (Randomization)		
CFS		
BMI		
Comorbidities		
Diabetes		
Hypertension		
CKD		
CLD/Cirrhosis		
CPD		
Heart Failure / CHD		
Immunocompromised		
Malignancy		
Smoker		
ARDS Diagnosis and Precipitating Factors		
PaO2 (mm/Hg)		
FiO2 (decimal)		
P/F Ratio		
PEEP/CPAP (cmH2O)		
Bacterial Pneumonia		
Viral Pneumonia		
Sepsis / Septic Shock		
Trauma-Related		
Transfusion-Related		
Inhalational Injury		
Pancreatitis		
ARDS Severity		
Mild		
Moderate		
Severe		

**Table 2 TAB2:** Dummy table showing primary and secondary outcomes ICU = Intensive Care Unit, LOS = Length of Stay, P/F = Ratio of Arterial Partial Pressure of Oxygen to Fraction of Inspired Oxygen, VFD = Ventilator-Free Days, CI = Confidence Interval

Variable (mean±SD) or (n,%)	Furosemide Group (n=………)	Control Group (n=………..)	Mean/Percent difference (95% CI; p-value)
ICU Mortality Within 28 Days			
Hospital Mortality			
ICU LOS			
Hospital LOS			
P/F Ratio Change Within 7 Days			
28 Days VFD			
Successful Extubation			
Adverse Events			

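### The primary outcome counts only deaths inside the ICU, while the hypothesis and analysis speak of 28-day mortality, so an observed ward death before day 28 scores as survival

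*Protocol article*

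**What the plan says.** Three places tie the primary outcome to the ICU:

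- Abstract: "The primary objective of this study is to analyze 28-day all-cause ICU mortality".
- Study objectives: "The primary objective is 28-day mortality in the ICU, starting from the day of randomization".
- Dummy Table 2, first row: "ICU Mortality Within 28 Days".

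Other places name death by day 28 without a location:

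- Introduction, hypothesis: furosemide "may decrease 28-day mortality".
- Statistical plan: the chi-square comparison for the primary outcome is of 28-day mortality, with no mention of the ICU. The survival data are described as follows: "Time-to-event data will be 28-day mortality as the event and duration since randomization as the time variable, with right censoring".
- Study objectives, VFD rule: "patients still mechanically ventilated at day 28, or died by day 28, will be assigned zero VFD".

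On follow-up, Study design says that "the duration of follow-up will be till hospital discharge". All-cause hospital mortality is a secondary outcome. The sample size section assumes 40% control mortality and a 10-point reduction, and does not say whether these are ICU, hospital or all-location deaths, or by when.

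**The concern.** Two different endpoints are in play. The place where they part is the patient who leaves the ICU alive and dies before day 28. On the definition under Study objectives that patient is a survivor. On the hypothesis, and on a literal reading of the Statistical plan, the same patient is a death.

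The ICU limit is also a weak choice in itself. Leaving the ICU happens after randomization. The protocol hopes for faster recovery and leaves most management to the treating teams. If treatment changes when patients leave, it can change where deaths happen without changing how many happen. The primary test would then partly measure location. Even with no difference between arms, dropping deaths that occur elsewhere removes events and costs power if the planning rates included them.

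Two smaller matters follow from the follow-up rule. Deaths after hospital discharge but before day 28 are not observed. And the survival analyses use right censoring without a stated censoring time, so the handling of patients who leave alive before day 28 is open.

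**Working it through.** **1. Reproduce the planned size.** Inputs from the sample size section: 40% v 30%, 80% power, 5% type I error; tests are two-sided per the Statistical plan. With the pooled-variance formula and p̄ = 0.35,

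n = [1.960·√(2·0.35·0.65) + 0.842·√(0.40·0.60 + 0.30·0.70)]² / 0.10² = (1.322 + 0.565)² / 0.01 ≈ 355.9, so 356 per group and 712 in total.

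This matches the protocol. The arithmetic is sound; the open question is which deaths the 40% counts.

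**2. Power if 40% v 30% means all locations but only ICU deaths count.** Let f be the share of 28-day deaths outside the ICU, equal in both arms. The documents give no value for f, so it is an assumption. The recorded rates are 0.40(1−f) and 0.30(1−f), and

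power = Φ{ [Δ√n − 1.960·√(2p̄(1−p̄))] / √(p₁(1−p₁) + p₂(1−p₂)) }.

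For f = 5%, Δ = 0.095 and p̄ = 0.3325: (0.095·18.868 − 1.306)/0.663 = 0.734, so power is 76.9%.

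| f | Recorded rates | Power at 356 per group | n per group for 80% |
|---|---|---|---|
| 0 | 40.0% v 30.0% | 80.0% | 356 |
| 5% | 38.0% v 28.5% | 76.9% | 385 |
| 10% | 36.0% v 27.0% | 73.5% | 417 |
| 20% | 32.0% v 24.0% | 66.2% | 494 |

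**3. Bias if the share differs by arm.** Suppose true 28-day mortality is 40% in both arms (an illustration).

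- Shares of 10% (control) and 20% (furosemide): recorded 0.40·0.90 = 36% v 0.40·0.80 = 32%, a false 4-point benefit. The chance of significance in that direction at 356 per group is about 20%.
- Shares of 10% and 25%: recorded 36% v 30%, with a chance of about 40%.
- Shares of 10% and 15%: recorded 36% v 34%, with a chance of about 8%.

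With no true effect, the chance in that one direction should be 2.5%. If the shares were reversed, the same mechanism would produce apparent harm.

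**4. Survival curves, only if patients are censored when discharged alive.** Take a proportion p who die and d who leave alive by day 28, constant hazards, and no deaths after discharge. Censoring at discharge gives

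1 − KM = 1 − (1 − p − d)^{p/(p+d)}.

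- p = 0.40, d = 0.20: 1 − 0.40^0.667 = 45.7%.
- p = 0.40, d = 0.40: 1 − 0.20^0.5 = 55.3%.
- p = 0.30, d = 0.50: 1 − 0.20^0.375 = 45.3%.

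So a true 40% would be shown as roughly 46-55% and would not agree with the chi-square proportion. The size depends on timing. With discharges uniform over days 7-28 and p = d = 0.40, simulation gives 53% for uniform death times, and 46% or 42% for truncated-exponential death times (mean parameter 10 or 5 days). The upward direction is the same each time. The between-arm difference hardly moves: for 40% v 30% true mortality with 40% v 50% discharged alive, it is 10.2-10.6 points in these simulations and 10.0 (55.3 − 45.3) under constant hazards.

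**The case against.** **The conflict may be shorthand.** Every place that defines or tabulates the primary outcome says ICU. The chi-square sentence in the Statistical plan opens by naming the primary outcome, so it can be read as pointing back to that definition. The VFD rule belongs to a separate secondary outcome and may count deaths more widely without contradiction. This largely stands, but it leaves the hypothesis unmatched and does not touch the design problem: on the ICU reading, a known ward death is scored as survival.

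**Ward deaths are not lost.** A reader might infer that ending follow-up at hospital discharge is what turns ward deaths into survivors. It is not. Follow-up to discharge records them, and hospital mortality would show them. The ICU restriction alone excludes them from the primary outcome. What the follow-up limit misses is death after hospital discharge and before day 28.

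**Censoring at discharge is not stated.** A reader might infer that the Kaplan-Meier, log-rank and Cox analyses are planned with informative censoring. The protocol gives no censoring time, and administrative censoring at day 28 is also right censoring. The remark under Study objectives that some patients are censored before seven days shows that earlier censoring is foreseen but gives no reason for it; the sample size section mentions transfers. The point therefore holds only conditionally. These are also supporting analyses, and step 4 shows little distortion of the comparison itself.

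**Faster discharge need not look like lower mortality.** That would need those patients to die outside the ICU by day 28. Double-blinding makes discharge decisions based on known allocation unlikely, although it does not stop a real treatment effect on discharge. Hospital mortality would help expose a shift, but it is a secondary outcome that the protocol itself says must not be taken as conclusive.

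**The recruitment target has a margin.** With all 392 per group analysed, the step 2 formula gives 83.7% at f = 0, and 80.7% and 77.5% at f = 5% and 10%. That margin is reserved for transferred patients, so it should not be spent on this.

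**Conclusion.** The point holds in this form. The primary outcome is restricted to ICU deaths, while the hypothesis and the analysis text carry no such limit, and the restriction discards deaths that the trial will observe. It can bias the primary comparison if the share of deaths outside the ICU differs by arm. If the share is equal at 5-10% and the planning rates are all-location, power at 356 per group falls to about 77-73%. If the 40% v 30% already refers to ICU deaths, there is no power loss on this account.

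The size and direction of any bias cannot be derived from the documents, because they give neither the share of deaths outside the ICU nor the rate of live discharge. Overstated Kaplan-Meier mortality follows only if patients are censored on leaving alive, and its size depends on assumed timing. If discharged patients were instead carried as event-free without a status check, unobserved deaths would count as survival.

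**What to change.** - Define the primary outcome in the Abstract, Study objectives, Statistical plan and Table 2 as all-cause death by day 28 after randomization, in any location, to match the hypothesis.
- For patients discharged or transferred before day 28, obtain day-28 vital status from records or a phone call. Add a sensitivity analysis for those whose status stays unknown rather than assuming that they are alive.
- In the Kaplan-Meier, log-rank and Cox analyses, censor patients known to be alive at day 28 administratively at day 28, not at discharge.
- Keep ICU mortality and hospital mortality as secondary outcomes.
- State which outcome, place and time point the 40% control rate describes. If it is all-location 28-day mortality, 356 per group remains right.

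The cost is a wording change in the protocol and registry entry, and a status check for early discharges and transfers. Ward deaths in the study hospital need no new data collection.

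### P/F change leaves out patients censored before day 7 and length of stay has no rule for death, so both secondary comparisons can be distorted by mortality

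*Protocol article*

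**What the plan says.** All references are to the Protocol article.

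- **P/F ratio.** Study objectives lists "the difference in P/F ratio between day one and day seven (not to be calculated for patients who are censored before seven days" as a secondary outcome. Censoring is not defined there. The Statistical plan mentions it only for survival: "Time-to-event data will be 28-day mortality as the event and duration since randomization as the time variable, with right censoring".
- **Length of stay.** Study objectives lists "ICU and hospital length of stay (LOS") without saying how a patient who dies is counted.
- **Ventilator-free days.** The same section does give this outcome a death rule: "patients still mechanically ventilated at day 28, or died by day 28, will be assigned zero VFD".
- **Test.** The Statistical plan applies one rule to all continuous secondary outcomes: "while continuous variables will be compared between groups by the student's t-test or the non-parametric Wilcoxon Rank-Sum test".
- **Analysis principle.** "Data of the patients will be analyzed in the group to which they were randomized, regardless of the actual intervention they received".
- **Supporting analyses.** The regression models and the per-protocol analysis are for the primary outcome only. Dummy Table 2 shows P/F change and both LOS outcomes as simple group differences with a confidence interval and p-value.

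**The concern.** Whether a patient has a day-7 P/F value is settled after randomisation, at the least by whether the patient is alive. Death is what the trial hopes to change. If the drug alters early mortality, the two sets of patients with a P/F change differ in make-up even if the drug does nothing to oxygenation, and randomisation no longer protects the comparison.

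LOS has a related problem. Someone who dies on day 3 contributes a three-day stay, which a t-test or rank test cannot tell from a three-day recovery. With control mortality planned at 40%, this concerns a large share of the data. The authors handled the same problem for VFD but not for the two LOS outcomes listed beside it.

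At stake is the reading of the secondary results. A drug that met its mortality target could be reported as prolonging stay, or as doing less for oxygenation than it does. The Introduction cites P/F change and hospital LOS as favourable trends in the earlier COVID-19 trial, so readers are likely to look at both here.

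**Working it through.** **Figures from the plan.** Sample size calculation gives mortality of 40% versus 30%, 80% power, 5% type I error and 392 per group. The tests are two-sided. The plan's own figure reproduces:

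n = [1.960·√(2·0.35·0.65) + 0.842·√(0.40·0.60 + 0.30·0.70)]² / 0.10² = 356 per group, 712 in total; 356 × 1.10 = 391.6, rounded up to 392.

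The plan gives no figure for P/F or LOS, so the inputs below are assumptions unless attributed to the plan.

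**1. P/F change, no true drug effect.** Assumed: SD 70 mmHg; deaths by day 7 of 20% (control) and 15% (furosemide); a standard normal health score with correlation ρ = 0.3 to 0.7 with P/F change; deaths are the lowest scores.

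*Deaths alone removed.* The mean score of those remaining is φ(a)/(1 − d), where d is the death proportion and a its normal quantile.
- Control: 0.2800/0.80 = 0.350
- Furosemide: 0.2332/0.85 = 0.274
- Difference −0.0756; times 70ρ gives **−1.6, −2.6 and −3.7 mmHg** at ρ = 0.3, 0.5 and 0.7
- Standard error: 70·√[1/(392·0.80) + 1/(392·0.85)] = 5.5 mmHg

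*Early recoverers also removed* (assumed 25% control, 30% furosemide, the highest scores). The mean becomes [φ(a) − φ(b)]/0.55, with b the upper cut-off. Each arm keeps 55%.
- Control: (0.2800 − 0.3178)/0.55 = −0.069
- Furosemide: (0.2332 − 0.3477)/0.55 = −0.208
- Difference −0.139; times 70ρ gives **−2.9, −4.9 and −6.8 mmHg**
- Standard error: 70·√[2/(392·0.55)] = 6.7 mmHg

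A second, simulated model used a severity effect of 25 mmHg per SD, residual SD 50 and the same day-7 deaths. It gave −1.2 mmHg from deaths alone and −3.4 mmHg when early extubation (25% versus 35%) also removed patients. With equal deaths and equal extubation it gave essentially zero.

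**2. Length of stay, no effect on stay given survival or death.** Planned mortality, with assumed mean stays of 10 days (deaths) and 20 days (survivors):
- Control: 0.40·10 + 0.60·20 = **16 days**
- Furosemide: 0.30·10 + 0.70·20 = **17 days**

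Simulation with 392 per arm, lognormal stays (log-SD 0.6) and 2,000 trials per row:

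| Mortality | Median stay, survivors / deaths | Mean difference | Wilcoxon p<0.05 | t-test p<0.05 |
|---|---|---|---|---|
| 40% vs 30% | 16 / 6 days | +1.2 days | 46% | 30% |
| 40% vs 30% | 16 / 8 days | +0.9 days | 28% | 21% |
| 40% vs 30% | 14 / 10 days | +0.5 days | 11% | 10% |
| 40% vs 30% | 12 / 12 days | 0 | 4% | 4% |
| 40% vs 40% | 16 / 8 days | 0 | 5% | 5% |

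The LOS distortion therefore needs both a mortality difference and a difference in stay between those who die and those who survive.

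**The case against.** Several points on the other side have force.

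- **Early recoverers.** A reader might infer that the P/F rule drops everyone who recovers early, and so close to half the trial. The text does not say so. Study design runs follow-up to hospital discharge, the only loss the sample size section names is transfer to another facility, and under Study intervention extubation ends the study drug, not follow-up. Losing early deaths is the natural minimum; anything beyond that hangs on an undefined word.
- **Size and direction for P/F.** From deaths alone the bias stays below one standard error, and even the widest reading only reaches about one. The direction is assumed too. The outcome is a change, and patients who start lowest have the most room to rise, so extra sick survivors need not lower the mean.
- **Intention to treat.** A reader might call the P/F rule a contradiction of the ITT statement. The plan defines ITT as analysis by assigned group, and nobody is moved between groups. The issue is selection after randomisation.
- **Change score.** Not adjusting for baseline P/F costs precision, not validity.
- **LOS rests on silence.** Detail on deaths could sit in an analysis plan that is not shown, and Table 2 prints mortality and VFD beside LOS. But the test is already fixed, and the VFD rule shows that this article sets a death rule where its authors wanted one.
- **Secondary status.** The plan says secondary outcomes are not conclusive. Its reason is multiplicity, which neither warns of nor corrects a systematic bias.

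**Conclusion.** The point holds in a limited form and should be addressed. Followed as written, the plan compares P/F change in a subset defined by events after randomisation, and compares LOS in a way that counts early death as a short stay.

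For P/F the likely distortion is modest: about 1.6 to 3.7 mmHg from deaths alone and about 3 to 7 mmHg if early recoverers are also excluded. Both ranges rest on the assumed SD, event rates and correlations. In the scenarios computed the bias runs against an effective drug, but the documents do not support stating that direction as certain.

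For LOS the distortion could matter more. At the planned mortality difference it is about one day under the 10- and 20-day assumption. In the simulations with unequal stays, between 11% and 46% of trials gave a significant Wilcoxon result with no effect on stay itself. It vanishes if stays, or mortality, are equal.

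The documents do not support extending the criticism to the primary outcome or the sample size.

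**What to change.** **P/F ratio.** Define censoring for this outcome so that extubation alone does not remove a patient who is still under follow-up. Keep the change among patients measured on day 7 as a descriptive result. Base the between-arm comparison on ranks in all randomised patients: death before day 7 ranks worst, patients liberated alive rank best, and those still ventilated on day 7 rank between by their P/F result. State a rule for patients transferred out, for whom the plan allows 10%, and class re-intubated patients by their status on day 7.

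**Length of stay.** Base the between-arm test on ICU-free and hospital-free days to day 28 with death scored zero, mirroring the VFD rule. Because follow-up ends at hospital discharge, state a convention for status between discharge and day 28. Report raw ICU and hospital LOS descriptively by survival status.

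**Cost.** This is mainly wording, but not only that. The registered secondary outcomes need an update before unblinding; the existing ones can stay as descriptive results. The P/F result becomes a rank comparison rather than a difference in mmHg, and it partly overlaps mortality and VFD. The post-discharge convention is either an assumption or a small extra data item.
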